**Study Measurement Schedule**

| **Measurements** |  | | |
| --- | --- | --- | --- |
| **Week ** | Baseline | **2** | **3** |
| Initial Screening |  |  |  |
| Study specific questions |  |  |  |
| Height |  |  |  |
| Weight |  |  |  |
| Waist circumference |  |  |  |
| 24-Hour Recall (AMPM) |  |  |  |
| Physical activity(PAR-Q) Pedometers |  |  |  |
| Accelerometry |  |  |  |
| Pedometry |  |  |  |
| Post-study survey |  |  |  |

# Intervention schedule

| **Days ** | 1 | 2 | 3 | 4 | 5 | 6 | 7 | 1 | 2 | 3 | 4 | 5 | 6 | 7 | 1 | 2 | 3 | 4 | 5 | 6 | 7 |
| --- | --- | --- | --- | --- | --- | --- | --- | --- | --- | --- | --- | --- | --- | --- | --- | --- | --- | --- | --- | --- | --- |
| **Intervention group**  Accelerometers distribute/return |  |  |  |  |  |  |  |  |  |  |  |  |  |  |  |  |  |  |  |  |  |
| Education materials |  |  |  |  |  |  |  |  |  |  |  |  |  |  |  |  |  |  |  |  |  |
| Pedometers distribute/return |  |  |  |  |  |  |  |  |  |  |  |  |  |  |  |  |  |  |  |  |  |
|  | | | | | | | | | | | | | | | | | | | | | |
| **Control group**  Accelerometers distribute/return |  |  |  |  |  |  |  |  |  |  |  |  |  |  |  |  |  |  |  |  |  |
| Education materials |  |  |  |  |  |  |  |  |  |  |  |  |  |  |  |  |  |  |  |  |  |

**Intervention Phase**

The study will take place over a period of 30 days. After randomization, participants will be assigned to either the intervention or control group. Participants will be asked about their usual diet. They will then be asked to wear an accelerometer (a device that measures physical activity and inactivity) for 7 days (one week). When they return, they will be asked about their physical activity. The next 7 days (one week), both groups will receive culturally tailored educational materials (Appendix E) about how to become physically active. Participants assigned to the intervention group will receive a pedometer along with directions about how to use it to help increase their physical activity. They will be asked to write down the number of steps taken each day they wear the pedometer. The last 7 days (one week), the intervention group will be asked to wear the accelerometer again and also a pedometer. The control group will be asked to only wear the accelerometer again. When participants in the intervention group return the accelerometers, they will be asked about their experiences over the previous few weeks. Directions and personal instructions will be provided on how to use the pedometer as a self-monitoring tool to increase the number and intensity of steps participants take each day to increase the probability of meeting the DG physical activity recommendations. Examples will be provided of walking paces that correspond to moderate-to-vigorous physical activity to help ensure that walking is undertaken at a suitable intensity**.** Self-monitoring will be enhanced by having participants keep a daily log of the number of steps they take each day when they rest their pedometer.

**Limitations of the Intervention**

The potential limitation and/or problems to be anticipated include non-compliance and loss to follow-up. To minimize this effect, Walmart gift card in the amount of $30 will be given to all study participants.In addition, all participants will receive a pedometer to keep as an incentive.

Study Design

We will conduct a randomized controlled trial to determine the feasibility of using pedometers to cause immediate short-term increases in moderate-to-vigorous physical activity in the Lower Mississippi Delta population.

#

Subjects

# A total of 60 adults (men and women 35 - 64 years of age) living in Point Coupee Parish, Louisiana will be recruited and randomized to either the control or intervention group.

**Data Management**

Each participant will be issued an assigned ID number that will be utilized throughout the intervention. A secure master file linking names, addresses and ID numbers will be maintained in a confidential computer file accessible only to the Principal Investigator. Access to data files can be made only with permission of the Principal Investigator. The nutritional epidemiology, biostatistics, and computer administration sections at the Pennington Biomedical Research Center will provide support for data collection and management, including data forms, on-site data management and data transfer. Privacy in the context of this study includes confidentiality of data and personal information. During interviews and measurements, the intervention staff will ensure full privacy of participants and will ensure that the data are stored in a secured area. All intervention staff must be HIPAA certified. Only trained and certified examiners will collect data. The PBRC Biostatistics Department will cooperate with [name], the data manager, who will manage the data entry into the clinical database to ensure quality of data.

**Randomization Process:**

Each eligible volunteer who is accepted into the study will be randomized to one of two levels of treatment. Randomization will be done by the PBRC Biostatistics group and results will be stored in the study database and transmitted back to the investigators.

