## **STUDY PROCEDURES**

**I) Baseline (Formative) Research.** During this time, we will publicly meet with community members to introduce the study. In addition, the intervention-site for the study will be determined.

**II) Study Training.** The investigators will provide training of staff for study implementation. At least one day of training will be conducted at PBRC in study procedures including protocol, consent, anthropometric measurements, dietary recalls, physical activity (including accelerometers and pedometers).

**III) Recruitment of Study Participants and Screening.** The goal for the feasibility study is to recruit a total of 60 males and females utilizing public service announcements (radio and TV), print (church bulletin announcements, and verbal announcements made by Pastors of churches in Pointe Coupee Parish during each church worship service, local community events, auxiliary meetings, word-of-mouth, presentations to various groups and organizations, and flyers (Appendix A) distributed at various businesses and churches throughout Pointe Coupee Parish. Recruitment and screening of study participants will be conducted using specific study criteria. A screening form designed to select eligible and exclude ineligible individuals will be utilized for the study. Recruitment for the feasibility study will begin on January 4, 2010 and end once 60 males and females are enrolled in the study. Baseline data collection will begin prior to the start of the study. We plan to conduct this study in Pointe Coupee Parish, LA. If we fail to achieve adequate sample sizes, we will begin recruiting subjects from adjoining Parishes, in particular, Avoyelles Parish.

**IV) Enrollment and Consent Procedure.** After screening, eligible subjects will be formally enrolled into the study. Each subject will be asked to sign an IRB-approved written informed consent form which details the purpose of study, the requirements for participation, and the potential benefits and risks. It will also indicate that participation is voluntary and may be terminated by the participant at any time. After the informed consent is obtained, baseline measurements will begin.

**V) Measurements.** All measurements will be conducted by designated staff. The following measurements will be made in all study participants as listed below:

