# Steps to Increase Physical Activity

# Study Specific Questions

## Adults (Males & Females) BMI **25 – < 35**

**Age 35-64 years**

### Design: 60 Volunteers (30 control group; 30 intervention group) for 3 weeks, 7 days each week.

#### YES NO

1. Do you have heart disease? ____ ____

2. Do you have diabetes? ____ ____

3. Do you have high blood pressure? ____ ____

If so, what medication are you on? **(Hytrin excludes) ____________________________**

4. Are you on cholesterol medication? ____ ____

5. Are you on a medically supervised diet? ____ ____

6. Have you ever been diagnosed with an eating disorder? ____ ____

7. Have you ever had a stroke? ____ ____

1. Have you ever been diagnosed with cancer? ______ ______

9. Have you ever had Hepatitis B, C, or HIV? ____ ____

10. Do you have or ever had tuberculosis? ____ ____

11. Are you currently enrolled in any other study? ____ ____

12. Are you planning to move from area in next 30 days? ____ ____

13. Has your doctor told you to limit physical activity? ____ ____

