**What is the total number of people living in your household?**

1. 1 

2. 2 

3. 3 

4. 4 

5. 5 

6. 6 

7. 7 or more 

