**Next steps**

[figure not shown]
 Record only the time you are *doing* the activity (Don’t include breaks).

[figure not shown]
 Achieve your target goals.

[figure not shown]
 Walk (or do something like walking) to achieve the physical activity recommendations.

If you have a concern about too much too soon, then start slowly and work up to the recommendation at your own pace**.**

- Include a friend or family member if you like.
- Plan activities you LIKE to do.

Make a **plan for how active you will be** next week:

|  | **What I will do** | **When** | **Minutes** |
| --- | --- | --- | --- |
| Monday |  |  |  |
| Tuesday |  |  |  |
| Wednesday |  |  |  |
| Thursday |  |  |  |
| Friday |  |  |  |
| Saturday |  |  |  |
| Sunday |  |  |  |
| **Total minutes for the week (30 minutes or more):** | | |  |

EXERCISE AND FITNESS WEBSITES

[www.aahperd.org](http://www.aahperd.org/) American Alliance for Health, Physical Education, Recreation, and Dance. Provides links to American Association for Active Lifestyles and Fitness, American Association for Health Education, American Association for Leisure and Recreation, National Association for Girls and Women in Sport, National Association for Sport and Physical Education, and the National Dance Association.

[www.acsm.org](http://www.acsm.org/) American College of Sports Medicine. This is the homepage of the largest, most respected sports medicine and exercise science organization in the world.

[www.acefitness.org](http://www.acefitness.org/) American Council on Exercise. This not-for-profit organization sets certification standards for exercise professionals and runs a consumer fitness hotline offering referrals to ACE certified personal trainers. Their web site features information about their programs, referrals to fitness resources and news about exercise and fitness.

[www.cascade.org](http://www.cascade.org/) This site is loaded with bicycling websites all over the world. Nearly anything you might want to know regarding bicycling can be accessed from this page.

[www.fitnessworld.com](http://www.fitnessworld.com/) This site provides information about exercise books and videos, recent news highlights related to health and fitness, and answers to frequently asked questions about fitness.

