**Strategies for increasing your physical activity easily:**

- park farther from the office entrance
- take the stairs (up and/or down) instead of elevators
- walk to lunch
- take the dog for a walk
- go for a walk in the evenings with your spouse
- leave the car at home and walk to the convenience store
- walk around the shopping mall

***Attached are some instructions for recording your minutes of physical activity. Please review these instructions and complete the calendar by recording as indicated.***

Written Instructions

Pedometer

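### Volunteers are randomised one by one with no rule for those who share a household, so any couple that co-enrols can be split between arms and the pedometer contrast biased toward zero

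*Protocol*

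**What the plan says.** **Unit of allocation.** The Randomization Process section says: "Each eligible volunteer who is accepted into the study will be randomized to one of two levels of treatment". It has no provision for couples, relatives or people at one address. Appendix C gives the design as "60 Volunteers (30 control group; 30 intervention group) for 3 weeks, 7 days each week".

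**Recruitment.** Study Procedures, item III, seeks men and women in Pointe Coupee Parish. Its channels include "verbal announcements made by Pastors of churches in Pointe Coupee Parish during each church worship service" and "word-of-mouth, presentations to various groups and organizations", alongside radio, television, print and flyers.

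**What each arm receives.** Under Intervention Phase, "both groups will receive culturally tailored educational materials"; only the intervention group also gets a pedometer and directions for using it. The education material in Appendix F, which goes to both arms, says under Next steps: "Include a friend or family member if you like". The pedometer sheet among the Study Forms lists, as one of several strategies, "go for a walk in the evenings with your spouse".

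**Information on links between participants.** Appendix C asks "What is the total number of people living in your household" but not whether anyone else there is taking part. Appendix B records last name, mailing address, apartment and home telephone. The Limitations section anticipates non-compliance and loss to follow-up; it does not mention contamination. The Post-Study Survey does not ask about exercising with another participant.

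**Analysis.** Statistical Analysis specifies Student's t-test on individual change scores for Hypothesis 1 and a permutation test on change in percent achievers for Hypothesis 2.

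**The concern.** Because both arms receive the education material, the randomised contrast is the pedometer and its directions and nothing else. Those directions set a step goal and a walking pace, and the outcome is minutes of moderate-to-vigorous activity on each participant's own accelerometer. A control who regularly walks beside a pedometer user can record some of the same minutes without touching the device. The control arm's change then rises and the difference shrinks.

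Recruitment through congregations and word of mouth makes it plausible that some volunteers know or live with one another, and the age and sex criteria allow both members of a couple to qualify. Individual allocation would then split about half of such couples. The unit of allocation is fixed in the Protocol; once the list has been used, an analysis plan cannot undo the mixing.

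Couples also affect the analysis. The t-test treats everyone as independent, which two members of one household may not be.

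**Working it through.** The Protocol gives no power, standard deviation, baseline mean or contamination rate, so there is no figure of its own to reproduce. The steps below scale the risk.

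**Inputs**
- From the Protocol (Appendix C): 60 volunteers, 30 per arm.
- From the Protocol (Randomization Process): individual allocation.
- Assumed: k couples enrol, k = 0 to 15.
- Assumed: a control whose partner is in the pedometer arm takes up a fraction u of the pedometer effect, u = 0.5 to 1.

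**Step 1: chance that a couple is split.** Once one partner is placed, 59 places remain, 30 of them in the other arm: 30/59 = 0.508, or 51%.

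**Step 2: share of controls affected.** Each split couple puts one control with a pedometer-using partner. The expected number is k × 30/59, and as a share of 30 controls, s = (k × 30/59)/30 = k/59.

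**Step 3: attenuation.** If the true effect is δ, the affected controls raise the control mean by s × u × δ, so the expected contrast is δ(1 − s × u). The attenuation is s × u.

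| Couples k (assumed) | Controls affected | Share s | Attenuation, u = 0.5 | Attenuation, u = 1 |
|---|---|---|---|---|
| 0 | 0 | 0% | 0% | 0% |
| 2 | 1.0 | 3.4% | 1.7% | 3.4% |
| 5 | 2.5 | 8.5% | 4.2% | 8.5% |
| 10 | 5.1 | 16.9% | 8.5% | 16.9% |
| 15 | 7.6 | 25.4% | 12.7% | 25.4% |

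Attenuation is proportional to u, so uptake below one half gives proportionately less.

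**Step 4: what that means for power (illustration only).** With 30 per arm, a two-sided 5% t-test (the Protocol gives 0.05 but not the sidedness) has 80% power for an effect of 0.736 standard deviations. Attenuation of 5%, 10% and 20% leaves 0.699, 0.662 and 0.588 standard deviations, and power of 76%, 71% and 61%.

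**Step 5: precision cost of allocating households together.** If a fraction f = 2k/60 of participants are in pairs and ρ is the within-couple correlation of change scores, the variance of an arm mean is multiplied by about 1 + f × ρ. The Protocol gives no ρ. Since ρ cannot exceed 1, the multiplier is at most 1 + 10/60 = 1.17 for 5 couples, 1 + 20/60 = 1.33 for 10 and 1 + 30/60 = 1.50 for 15. With few couples or modest correlation it stays close to 1.

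**The case against.** The best case on the other side is that nothing in the Protocol shows this happening. A reader might infer that volunteers come from the same households, but no section says so: co-enrolment is merely not excluded, and radio, television, print and flyers are also used. Both partners would have to meet the age and body mass index limits and pass the medical questions in Appendix C, so 15 couples, half the sample, is an extreme assumption and zero is fully consistent with the text. This stands, and is why the range starts at 0%.

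A reader might also infer that the handouts instruct controls to exercise with pedometer users. They do not. The friend-or-family line is optional, the spouse line is one item in the pedometer sheet only, and neither refers to another participant. Nor does a walking companion receive the partner's step goal: that goal is built from the user's own baseline and pursued by checking the user's own device. What can pass across is shared walking time, over the two weeks after baseline. This stands too, and full uptake is therefore an upper limit.

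The forms do not leave households invisible, because Appendix B collects addresses. That makes the remedy easier but does not supply the missing allocation rule.

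Finally, merging every declared walking partner into one unit could chain members of a congregation into large clusters. That objection is sound, and the remedy should stop at the household.

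**Conclusion.** The point holds as a conditional weakness in the stated unit of randomisation. The Protocol recruits through social networks, suggests exercising in company, and has no rule for volunteers who live together. If couples enrol, about half will be split and the expected bias is toward zero.

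Its size cannot be established from the Protocol. Under the assumptions of 0 to 15 couples and 50–100% uptake, attenuation lies between 0% and about 25%; the top needs half the sample to enrol as couples and affected controls to take up the whole effect. The documents do not support saying that the contrast is diluted, only that it could be.

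A reader might go further and infer that a diluted result would wrongly keep pedometers out of the later effectiveness trial. The Protocol sets no go/no-go rule on the between-arm test. It says that lessons learned will inform the later design, and it takes step targets from intervention-arm data alone. The consequence is a less trustworthy estimate for Hypotheses 1 and 2, not a programmed wrong decision.

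**What to change.** **Randomization Process.** State that volunteers who share a household are randomised as one unit to the same arm. Identify them before allocation from the Appendix B addresses, and allocate both members at the same time, so that a later joiner does not already know the arm.

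**Participant instructions.** Ask all participants not to share pedometers or step goals until the final accelerometer has been returned.

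**Statistical Analysis.** For Hypothesis 1, replace the plain t-test with a model for change that has a household term, or use household-clustered standard errors. For Hypothesis 2, permute by household.

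**Walking partners outside the household.** Record them, but do not merge them into units. Contamination through wider church or friendship ties is then documented, not prevented.

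**Cost.** An address check before allocation, a change to the allocation list and a few sentences of text. Arm sizes may differ slightly from 30/30, and pairing costs some precision, which is small when couples are few. If no couples enrol, the allocation and analysis are in effect those now planned.

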**Data Entry**

Double entry will be used for all manual entry of data to help ensure the fidelity of the database; scanable forms used wherever possible to minimize the need for manual data entry. The PBRC Data Management Group will have the prime responsibility for database design and implementation, programming, coordination and manual data entry of the study data into the study database.

**Statistical Analysis**

Analyses will be performed using SAS software. In the case of missing data, several approaches will be used, including an analysis restricted to participants with complete data; a last observation carried forward analysis, and a mixed model analysis. Sensitivity of analytical results to these alternative approaches will be assessed. Statistical tests that result in p-values ≤0.05 will be considered indicative of statistical significance.

The focus of the statistical analysis for **Hypothesis1** will be on comparing intervention and control groups with respect to changes in accelerometer-measured physical activity from the 7-day baseline (pre-intervention) assessment to the 7-day follow-up (post-intervention) assessment. Physical activity (minutes of moderate-to-vigorous physical activity) will be summarized as group means and 95% confidence intervals, separately for baseline and follow-up assessments. Student’s t-test will be used to assess statistical significance of differences in group means for individual physical activity change scores = post-score ─ pre-score. Although this is a feasibility study, we feel that a clinically significant increase in number of daily minutes of moderate-to-vigorous physical activity in this sedentary population would be a 100% increase.

The focus of the statistical analysis for **Hypothesis 2** will be on comparing intervention and control groups with respect to possible increase in percentage of participants achieving DG physical activity recommendations. The (nonparametric) permutation test will be used to assess differences in change in percent achievers in intervention vs. control groups (the sample sizes in this feasibility study are not sufficient to justify employing chi-square tests). Although this is a feasibility study, we feel that a clinically significant increase in the proportion of participants achieving the DG physical activity recommendations will be a doubling of the baseline proportion.

The focus of the statistical analysis for **Non-Hypothesis 3** will be on determining the number of steps associated with reaching the DG physical activity recommendations of 60 minutes a day of moderate-to-vigorous physical activity. General linear mixed models will be used to assess the cross-sectional relationship between daily number of steps (from pedometer) and minutes of moderate-to-vigorous physical activity (from accelerometer) using data collected post-intervention on all subjects in the intervention group. A mixed model approach is required to incorporate all seven days worth of data collected on each participant. The number of steps corresponding to 60 minutes of moderate-to-vigorous physical activity will be determined, and potential gender differences in the target number of steps will be examined. If significant gender differences exist, gender-specific step targets will be calculated and used in the future effectiveness study.

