**Waist Circumference**

**Procedure**

Instruct the participant to gather his or her shirt above the waist, cross the arms, and place the hands on opposite shoulders. Demonstrate the desired position of the arms. It may help to tell participants to think of giving themselves a hug. If necessary, lower the pants and underclothing to slightly below the waist. Again, always tell the participant what you are going to do before you do it.

Stand on the participant’s right side. Palpate the hip area to locate the right ilium of the pelvis. With the cosmetic pencil draw a horizontal line just above the uppermost lateral border of the right ilium. Cross this mark at the midaxillary line, which extends from the armpit down the side of the torso. Exhibit 3-9 shows the measurement site correctly marked for the waist circumference.

Extend the measuring tape around the waist. Position the tape in a horizontal plane at the level of the measurement mark, and ensure the horizontal alignment of the tape. Check that the tape sits parallel to the floor and lies snug but does not compress the skin. Always position the zero end of the tape below the section containing the measurement value. Take the measurement to the nearest 0.1 cm at the end of the participants.

4. Physical Activity Assessment. Study participants will be asked to respond to a physical activity readiness questionnaire (PAR-Q) [Appendix E) for safety reasons before beginning any physical activity regime. Accelerometers and Pedometers will be provided and used to measure physical activity and to increase steps.

Acceleromter Procedure

The ActiGraph accelerometer will be used to determine physical activity at baseline and at follow-up as follows:

The measurement of physical activity pattern and volume, specifically minute-by-minute participation in different intensities of physical activity. The equipment used is the ActiGraph GT3X manufactured by ActiGraph, of Ft. Walton Beach, FL ([www.theactigraph.com](http://www.theactigraph.com/)), and previously distributed as the GT1M, the 7164, the MTI, and the CSA. An ActiGraph User Manual is also available for download from this website.

Process Overview

1. Charging accelerometer
2. Initializing accelerometer (preparing the device to collect data)
3. Instructing the participant on self-monitoring procedures
4. Downloading data
5. Preparing electronic files for archiving

Procedure

1. Charging accelerometer

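### Hypothesis 1: the unadjusted change-score t-test is valid but can be less precise than baseline adjustment, and LOCF with a single follow-up week imputes zero change

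*Protocol*

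**What the plan says.** The Statistical Analysis section compares the arms on change in accelerometer-measured activity "from the 7-day baseline (pre-intervention) assessment to the 7-day follow-up (post-intervention) assessment". The test is Student's t-test, which "will be used to assess statistical significance of differences in group means for individual physical activity change scores", defined as post minus pre. No covariate is mentioned.

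For missing data, "several approaches will be used, including an analysis restricted to participants with complete data"; the other two are "a last observation carried forward analysis, and a mixed model analysis". The section adds: "Sensitivity of analytical results to these alternative approaches will be assessed".

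The outcome is measured twice. The accelerometer procedure states: "The ActiGraph accelerometer will be used to determine physical activity at baseline and at follow-up". The Intervention Phase section agrees: the device is worn in the first week and again in the last, and not in the week between. Appendix C gives the size as "60 Volunteers (30 control group; 30 intervention group) for 3 weeks, 7 days each week".

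Two other statements matter. Limitations of the Intervention expects some loss to follow-up but gives no rate. Intervention Phase gives the educational materials to both arms, so controls may change too.

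**The concern.** Two choices fixed in the text deserve a second look.

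- **Precision.** A change-score comparison assumes that each extra baseline minute predicts exactly one extra follow-up minute. A model that estimates this slope from the data usually has a smaller residual variance. With 30 per arm, precision that costs nothing is worth having.
- **LOCF.** The method is usually applied to several post-baseline visits. Here there is one, so the value carried forward is the pre-intervention week. The analysis then states that a person who was not measured did not change. This alters the estimated arm difference whenever the true changes are not zero.

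At stake are the size and reliability of the estimate that this feasibility study passes to the planned effectiveness trial.

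**Working it through.** The protocol gives no SD, pre-post correlation, effect in minutes, dropout rate or power calculation, so there is no stated figure to reproduce. From the documents come 30 per arm, two assessments, a change-score t-test and LOCF. Everything else below is an assumption, shown as a range where possible.

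**1. Precision.** Let ρ be the pre-post correlation and k = SD_post/SD_pre, with variances in units of SD_pre².

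- Change score: 1 + k² − 2ρk
- Baseline-adjusted: k²(1 − ρ²)
- Difference: (1 − ρk)², which is never negative and is zero when SD_pre = ρ·SD_post

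With k = 1 these are 2(1 − ρ) and 1 − ρ², and their ratio is 2/(1 + ρ).

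| Variance ratio, change/adjusted | ρ = 0.4 | ρ = 0.6 | ρ = 0.8 |
| --- | --- | --- | --- |
| k = 1 | 1.20/0.84 = 1.43 | 0.80/0.64 = 1.25 | 0.40/0.36 = 1.11 |
| k = 1.5 | 2.05/1.89 = 1.08 | 1.45/1.44 = 1.01 | 0.85/0.81 = 1.05 |
| k = 2 | 3.40/3.36 = 1.01 | 2.60/2.56 = 1.02 | 1.80/1.44 = 1.25 |

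These ratios ignore the cost of estimating the slope, which is about 2% of the variance at N = 60. Where the ratio is 1.01 or 1.02, that cost cancels the gain.

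A simulation of 6,000 replicates (30 per arm, k = 1, ρ = 0.6, true difference 0.6 SD, nobody lost) gave power of 72% for the change-score t-test and 80% for the adjusted analysis.

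**2. LOCF.** Let Δ1 and Δ0 be the true mean changes in the intervention and control arms. Let m1 and m0 be the fractions with no follow-up week, with loss unrelated to the outcome within each arm. LOCF gives these people a change of zero, so its expected arm difference is (1 − m1)Δ1 − (1 − m0)Δ0.

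*Equal loss, true difference 8 min:*
- 10% lost: 0.90 × 8 = 7.2
- 20% lost: 0.80 × 8 = 6.4
- 25% lost: 0.75 × 8 = 6.0

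*Unequal loss, Δ1 = 12 and Δ0 = 4 min (true difference 8):*
- 20% lost in intervention, 5% in control: 0.80 × 12 − 0.95 × 4 = 9.6 − 3.8 = 5.8
- 5% lost in intervention, 20% in control: 0.95 × 12 − 0.80 × 4 = 11.4 − 3.2 = 8.2

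*No true difference, 5% lost in intervention and 25% in control:* if both arms rise by 0.5 SD, LOCF expects (0.95 − 0.75) × 0.5 = 0.10 SD in favour of the intervention. In simulation (ρ = 0.6) its type I error was 7.6%. For a common rise of 1.0 SD the figures were 0.20 SD and 14.7%. The complete-case t-test and the complete-case adjusted analysis stayed at about 5% in both settings.

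**The case against.** The case for leaving the plan alone is that it names a valid, unbiased test in advance, in a study that calls itself a feasibility study, and that adjustment is an efficiency preference. Much of this stands, and it rules out several stronger readings.

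- **That the baseline is wasted or the test is wrong.** The change score does use baseline, with a fixed coefficient. What is at risk is precision, not validity.
- **That the planned test is always clearly less precise.** The 2/(1 + ρ) factor needs equal SDs in the two weeks. The protocol regards a 100% increase in MVPA minutes as clinically significant, so a larger follow-up SD is plausible. In that case the gain may be negligible. A fixed sample-size equivalent for the 60 participants cannot be claimed.
- **That three unranked analyses allow three verdicts on Hypothesis 1.** One test is named. The three approaches apply only when data are missing, and the text says sensitivity across them will be examined. A statistical analysis plan may rank them.
- **That an interval for the arm difference is ruled out.** The section plans intervals for group means and does not exclude one for the difference. This too may be settled in an analysis plan.
- **That LOCF governs the result.** It is one of three analyses, and it forces zero change only where the whole follow-up week is missing. The written accelerometer instructions foresee single blank days, and the protocol does not say whether carrying forward works by day or by week. Carried within a week, it would not force zero change. The study is also short and offers incentives against loss.

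What remains is that both methods are fixed in the text. For a wholly missing follow-up week, LOCF can only carry the baseline forward.

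**Conclusion.** The point holds in limited form.

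The change-score t-test is valid. Apart from about one degree of freedom, it is never more precise than the adjusted analysis. The loss is 11% to 43% in variance for assumed correlations of 0.8 down to 0.4 with equal SDs, and close to nil when SD_pre is near ρ·SD_post.

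The LOCF problem follows from the design and needs no assumed correlation. Under equal loss the difference shrinks by the loss fraction. Under unequal loss, when both arms change, the bias can go in either direction, so LOCF cannot be defended as conservative. Its size depends on loss rates and changes that the protocol does not give, and it is zero if everyone returns a usable follow-up week.

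The trial's main test is not invalid. This is an avoidable weakness plus one prescribed analysis that does not suit a single follow-up.

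**What to change.** In the Statistical Analysis section:

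1. Make the Hypothesis 1 analysis a linear model of follow-up MVPA on arm and baseline MVPA.
2. If people without follow-up are to be kept, use instead a two-time-point mixed model with both weeks as outcomes and the baseline mean constrained equal across arms. The form matters. A model with baseline as a covariate drops anyone without follow-up, because that person has no outcome row. A two-time-point model with unconstrained baseline means gives the change-score estimate again on complete data.
3. Report the adjusted arm difference with its 95% CI.
4. Keep complete-case analysis as sensitivity and delete LOCF.

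The data and software stay the same. The cost is a few sentences of text and about one degree of freedom.
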